## Abstract

**Background:**

Exposure to second hand smoke (SHS) is a cause for heart disease and lung cancer among non- smokers. This cluster randomized control trial will evaluate the effectiveness of a tobacco smoke free home intervention in reducing exposure to second hand smoke.

**Protocol:**

The intervention will be conducted among 30 clusters in urban and peri-urban areas of Kochi, India. The sample size is 300 per arm and 15 clusters to detect a minimal difference of 0.03ng/ml in cotinine levels between groups, at 80% power with a two-sided alfa of 0.05 considering variable cluster size. A baseline survey will be undertaken to identify smokers. Data related to smoking, indoor smoking, nicotine dependence, blood pressure (BP) of smokers, morbidity experienced, and lung volume Fev1/Fev6 of smokers will be measured. Urine cotinine, morbidity, BP of spouse and child will be assessed. Air quality monitors measuring PM2.5 will be placed in homes. Trained self-help group women and frontline health workers will implement the intervention. The intervention will consist of monthly home visits to educate the smoker on the harms of second-hand smoke using 3 A’s. The circle of influencers around the smoking men will also be contacted by the members of self-help group to provide support to stop smoking within homes and to quit. They will then organize two-three meetings of community leaders and heads of women’s groups, present data on harms of SHS, and explain the rationale for establishing smoke free homes in their community for a duration of six months. After the intervention a post assessment will be conducted and this will be repeated after six months.

**Ethics and dissemination:**

The trial protocol was approved by the Institutional Ethical Committee of Amrita Institute of Medical Sciences. Results will be submitted to open access peer reviewed journals and shared with other stakeholders.

**Trial registration:**

CTRI/2021/06/034478

## Introduction

Noncommunicable diseases (NCD) are a major cause of morbidity and mortality in India. The disease transition in India in the past 2 decades is representative of the accelerated epidemiological transition model with a rapid shift to the age of delayed chronic diseases.
^
1
^ Therefore, in order to halt the epidemic of NCDs, not only should sick persons be treated, but healthy persons also need to be protected.
^
2
^

In Kerala, 90% of premature mortality in the 15-69 year age group is attributed to NCD.
^
3
^ Kerala also has the highest rate of coronary artery disease (CAD)
^
3
^ and diabetes in India, being in the most advanced stage of epidemiologic transition. Over the years the prevalence of Cardiovascular disease has seen an increase with cardiovascular disease accounting for 15.2% of total death in 1990 to 28.1% of total deaths in 2016 and more than half (53.4%) of crude deaths due to CVD were among people younger than 70 yrs.
^
4
^ While cardiovascular disease risk factors encompass diet, obesity, systolic blood pressure, and air pollution, tobacco use, despite its declining prevalence, consistently ranks among the top six risk factors.
^
4
^
^,^
^
5
^ Another risk factor study in Kerala pointed to the dismal fact that only a fifth of the study population; 20.4% of men and 16.5% were free of any of the seven NCD risk factors studied- tobacco use, alcohol use, obesity, abdominal obesity, raised BP, raised blood glucose or physical inactivity. Three or more risk factors were present in 20.9% and four or more NCD risk factors were present in 6.4% of the participants.
^
6
^

Globally, tobacco smoking including second-hand smoke (SHS), is one of the three leading risk factors for global disease burden, others being high blood pressure, and household air pollution from solid fuels.
^
7
^ Though there is a decline in the proportion of people exposed to domestic SHS in India, according to the recent Global Adult Tobacco Survey-2(GATS-2) report, it continues to be high at 38.2% among adults and 39.3% among women.
^
8
^ Being female, illiterate, poor, homemaker, resident of the rural areas was associated with the highest exposure to SHS at home in GATS-2.
^
9
^

Chronic exposure to SHS is suggested to be, on average, 80%–90% as harmful as chronic active smoking with a significant dose-response relationship.
^
10
^
^–^
^
12
^ SHS affects the heart and blood vessels, increasing the risk of myocardial infarction, stroke, and emotional changes like depression in non-smokers. Smokers’ children suffer reduced lung function, which continues to affect them in the form of chronic respiratory disorders in adulthood. School-aged children exposed to the harmful effects of second-hand smoke are also at risk for asthma through inflammation of the airways to the lungs.
^
13
^

Smoking regulations in public places such as hotels, theatres are prohibited and are governed by Section 4 of the Cigarette and other tobacco products Act (COTPA), 2003.
^
14
^ However, this alone has not resulted in substantial reductions in SHS exposure among women and children. The biggest source of involuntary exposure to tobacco smoke, particularly for children, is smoking by parents and other members of the household.
^
15
^ Smoking among children in the age group of 12-19 years was found to be higher among urban children and among those from poorer households.
^
16
^ There are also studies which point to the fact that those who report ever-use of tobacco are more likely to have experienced exposure to SHS at home.
^
17
^ Studies in urban areas of Kochi showed that SHS exposure from family members among higher secondary school students was 23.2%.
^
18
^ These are largely from men in the households as women smokers are very low (0.2%-2.2%) in Kerala.
^
19
^
^,^
^
20
^

There are about 300 slums and colonies in Kochi corporation and cardiovascular health issues are the third most common cause of morbidity according to the district government statistics.
^
21
^The formal health sector encounters slum residents only when they develop late-stage complications of preventable chronic diseases
^
22
^ due to competing priorities. Slums are a manifestation of the twin challenges of rapid urbanization and the urbanization of poverty.
^
23
^Despite a National Programme for control of Non-Communicable Diseases (NP-NCD) and laws like the Cigarette and Other Tobacco Products Act (COTPA), NCDs are increasing. Health outcomes are worse in slums and other impoverished settlements.
^
23
^
^,^
^
24
^ Therefore, in states like Kerala which has the highest burden of NCDs, progress in the control of tobacco control needs sustainable solutions embedded in the community. Due to high occupancy rates in all-purpose rooms in slums, smoking within homes can result in a high level of SHS exposure. Hence, the high population density is not only a risk factor but also an opportunity to efficiently reach a vulnerable proportion of the population.
^
24
^

Community embedded networks such as the “Kudumbashree” (which means welfare of the family) is a community network of women in the State of Kerala working in close coordination with the local self- government.
^
25
^ Throughout the world, diverse community leaders and organizations has been explored,
^
26
^
^–^
^
28
^ which were feasible with varying degrees of effectiveness. Moreover, a study on a community-based intervention by women’s self-help group members showed a significant reduction in blood pressure levels among people living in urban slums of Kerala, India.
^
29
^ Also, our initial experience from a smoke free initiative as part of ‘Quit Tobacco international activities’ suggests that “tobacco smoke free homes initiative” were feasible and a six week campaign with self-help group members brought a 30% decline in second hand smoking in a vulnerable fisherman community.
^
30
^ Therefore, intuitively, the potential impact of such interventions on reduction in second hand exposure and improvement of cardiovascular and respiratory health is large. It can also have tangible and intangible social and economic benefits. Hence this study plans to examine the effectiveness of an intervention partnering the self-help groups in reducing the second hand smoke exposure within homes.

Outcomes of the intervention need to measure exposure to second hand smoke. Biomarkers and indicators of environmental pollution were considered. Urinary cotinine level is a widely used biomarker and has a good correlation with daily tobacco consumption and second hand exposure.
^
31
^ Urine cotinine concentrations are more sensitive than in blood or saliva, making urine a sensitive matrix to detect low-concentration exposure.
^
32
^ Indoor particulate matter (PM), despite a background concentration of respirable particulate matter (PM) due to cooking and infiltration from outdoors, is considered a good indicator of SHS, at relatively high levels.
^
28
^
^,^
^
33
^ PM < 10 μm enter the respiratory tract, but may be the result of mechanical processes such as construction activities, road dust resuspension and wind whereas PM < 2.5 μm (fine particles) originate primarily from combustion sources such as smoking.
^
34
^ Quit rates and harm reduction are also outcomes which can be used to determine the impact of the intervention and will be reported as has been observed in other studies.
^
35
^
^,^
^
36
^

In order to assess the impact of the intervention on smokers perse FEV1/FEV6 was measured. This measure is a substitute for FEV1/FVC in diagnosing airflow obstruction and may better predict COPD-related pathology and morbidity.
^
37
^ The use of 6-s expiratory maneuvers makes handheld spirometry faster and easier, provides a more explicit end-of-test definition. Its use in primary care has also been demonstrated for the detection of COPD in adults.
^
38
^

Our intention is to enhance the application of evidence in the naturally occurring clusters which are the slums. Each of the slums is a unit with similar sociodemographic features where interventions can be more effective, compliance will be better and contamination less likely. We would like to capture the population level effects of the intervention. Thus, a cluster randomisation trial was chosen.

This study aims to assess the effectiveness of a “smoke-free home” intervention in partnership with women’s self-help groups in the slums of Kochi corporation, Kerala. This is a hybrid type 2 effectiveness-implementation research
^
39
^ combining the evaluation of effectiveness of the intervention and also assessing the implementation process. We hypothesize that a tobacco smoke-free home initiative in partnership with self-help group women will be effective in significantly reducing SHS in homes and SHS exposure among women and children of those homes over a period of 1 year. The specific aims are:
•To determine the effectiveness of an intervention led by women’s self-help groups to reduce indoor tobacco smoking by measuring urinary cotinine levels and reduction in indoor smoking by measuring PM 2.5 as an indicator for tobacco smoke in the home environment.•To correlate the urinary cotinine levels with the PM 2.5 in the indoor home environment.•To measure the effect of the intervention on the FeV1/FeV6 among smokers.•To explore the impact of the intervention on quitting rate, smoking intensity through in depth interviews and focus group discussions.

## Methods

### Sample selection

We have used the SPIRIT protocol according to guidelines. This will be a cluster-randomized community-based trial. Clusters will be slums with a population of more than 400 or 100 households in the Kochi Corporation and adjacent peri-urban areas. 30 clusters will be selected randomly from the sampling frame of 74 slums and colonies with a population of more than 400 population from a total list of 300 slums and colonies of Kochi Municipal Corporation and adjacent areas. These will be randomly assigned by a computer-generated table to the intervention or control arm with a 1:1 allocation ratio.

### Participants

*Eligibility*: All individuals who have been living in the area for more than 6 months are eligible to participate in the study. In the households the individuals will be screened to identify homes where the male members are between 18-80 years and smoke within the homes. Such male members will be considered for the study and a participation information sheet will be given following which informed written consent will be obtained. In order to determine the impact of passive smoking their spouse or a close female relative will be administered a questionnaire following informed consent. Similarly, children in the house less than 18 years will also be administered the child questionnaire and enrolled in the study after due consent from the legally authorised representative. If there are two children in the study the youngest child older than one years will be enrolled in the study. Single male migrants and household with transgenders will be excluded.

*Data collection*: Four semi-structured questionnaires have been developed and pretested. They include household, smoker, spouse and child questionnaires. The household questionnaire is for the household and comprises sociodemographic variables, number of family members, identifying the smokers, number of rooms, ventilation, distance from the road, type of road, any other source of air pollution within 500 m, organic and inorganic waste disposal, cooking fuel used, ventilation in the kitchen, use of mosquito coils, incense sticks, and the presence of pet animals. The smokers’ questionnaire will determine smoking habits, age of initiation of smoking, types of tobacco product used, money spent on tobacco per week, quit attempts, frequency and place of smoking within home, smoking when children are around, nicotine dependence score, awareness of harmful effects of second hand smoke, and who influences smokers the most. Nicotine dependence has been assessed by the Fagenstrom scale. The spouse questionnaire will consist of exposure to second hand smoke at home, practice of indoor smoking, ventilation in the kitchen, exposure to second hand smoke outside the home, cleaning habits, cooking practices, and medication use. The child questionnaire will consist of domains on reports of second-hand exposure at home and outside, history of respiratory morbidity in the past 6 months and history of hospital admission. For older children above 12 years the domains will also consist of history of tobacco use, age of initiation, and awareness regarding harm of second hand smoke. Standard methods of measurement of weight and height will be taken of the smoker, spouse and child. Blood pressure of the smoker and spouse will be measured by an electronic sphygmomanometer in a seated position after ensuring that the person is relaxed. If the reading is ≥140/90 mmHg the measurement will be repeated after 30 min and the average of the two will be taken. In order to measure FeV1/FeV6 the smokers will be instructed to take a deep breath and blow hard and long (6 seconds) till a beep is heard. The mouth should be sealed around the disposable mouthpiece. The measurement will be noted down by the health worker. We will also measure SHS through the air pollution monitor within the home which will measure particulate matter of size 2.5 microns and is a marker for the presence of SHS in the home. The device will be charged and left in the home for recording for 6-8 hours at an elevated place. The machine will record PM 2.5, 10 PM. The sensor will record the readings every 5 minutes and the output will be in the form of a graph. After downloading in the evening it will be given in the next house. This will be done at 6, 10, and 16 months respectively (
Table 1).

**Table 1. T1:** Data collection and outcome measures.

KIFT intervention (2)		Baseline (to)	Post- intervention (1)	Post-Intervention (2)
Demographic info		✓		
Tobacco use within homes		✓	✓	✓

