**Smoker**				
Smoking within homes (self-reports)		✓	✓	✓
Fagenstrom nicotine dependence score		✓	✓	✓
No of cigarettes smoked daily		✓	✓	✓
No of persons who have quit			✓	✓
Blood Pressure		✓	✓	✓
BMI		✓	✓	✓
Fev1/Fev6		✓	✓	✓
*Air pollution	PM 2.5	✓	✓	✓
	PM 10	✓	✓	✓
	CO _2_	✓	✓	✓
Women	Cotinine	✓	✓	✓
Child	Cotinine	✓	✓	✓
BMI	Child	✓	✓	✓
Resp. Infection	Child	✓	✓	✓
	Woman	✓	✓	✓
Process evaluation	In depth interview			✓
	FGD			✓

A door-to-door initial survey will be conducted following a training to the data collectors. After ascertaining the households where the male member smokes the interviews of the smoker, wife/close female relative, and child will be conducted. The interviews will be conducted separately for the husband and wife/close relative who is a woman. After the interview, Fev1/FeV6 ratio among the smokers will be assessed with the Vitalograph COPD-6 screener device. The women and child of the household will be asked to keep the urine sample in a sample bottle provided which is then placed in an auto seal pouch. These samples will be collected from all the houses and transported to the laboratory by maintaining cold chain at a temperature between 2-8 degrees C. The urinary cotinine levels among the women and children of the smoking households will be assessed in this urine sample. The cotinine levels will be assessed among the spouse of the smoker or among a woman who stays at home for a longer duration and a child up to 18 years of age. If there is more than one child in the house, the youngest child older than 1 year will be chosen. All houses may not have children; therefore, it is necessary to take both women and children’s cotinine levels. This would also be an important advocacy tool as the children’s cotinine levels can be used to influence the smoker. The urine cotinine level will be measured at 6, 10, and 16 months with the help of Cal biotech’s ELISA kit which will measure cotinine levels by ELISA (solid phase competitive ELISA). The test was calibrated and standardised in a pilot study among households of smokers and non-smokers and differences ascertained.

Quality of data collected will be ensured by training and retraining of the data collectors. The data collection forms are provided.
^
40
^
^,^
^
41
^ The laboratory tests will be carried out after validation. Data entry will be done with back up and range check-ups will be done for data values.

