**Figure 1. f1:**
[figure not shown]
Flow diagram for recruitment and follow up.

The training booklet (6-8 pages) has been developed for the ready reference of the SHG women who will deliver the intervention. The training booklet has been prepared by a team comprising a sociologist, health educator, communication specialist, community medicine expert, ASHA, and two SHG workers. The training booklet will be in an easy to understand form. The training booklet will consist of a review of the burden of the problem of tobacco, particularly smoking, the problem of second hand smoke, impact on women and children, and the use of the 3 A’s in the local language. They will also contain advice on the importance of not smoking within the home. The SHG/kudumbasree members will be partners in the development of communication material and will assist in the development of a poster, leaflet, and flip chart in order to ensure clarity, relevance, easy readability and understanding.

In the intervention clusters, an air quality monitoring committee will be formed to support the intervention. This will comprise of the SHG, ASHA, junior public health nurse (female health worker), ward councillor, and members of our team. This committee will guide the intervention. In the initial two months of the intervention the SHG-ASHA team will conduct monthly home visits for educating the smoker, spouse and others in the family on the harms of second-hand smoke using a flip chart. The circle of influencers around the smoking men will also be contacted by the members of the self-help group to provide support to quit. They will then organize a meeting of community leaders and heads of women’s groups, present data on harms of SHS, explain the rationale for establishing smoke free homes in their community, and ask for their assistance in arranging other educational meetings for community members. Two-three such educational meetings will be conducted per cluster where all the household members, particularly that of the smoking households, are encouraged to attend. These meetings will be conducted at different places in the community and doctors from the nearby primary health centres will come and talk about the harms of SHS and importance of becoming a smoke free home community. In these meetings other stakeholders, formal and informal leaders of the community, and local self- government representatives will be invited.

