In the next two months home visits will be conducted to paste the smoke free home stickers or distribute the calendars and reinforce the message of not smoking within homes and to get widespread recognition of the movement. Based on the findings of the baseline survey customized messages to quit will be delivered. The SHG-ASHA combined will also communicate the results of the cotinine levels and 2.5pm to the household members. The cotinine levels among the children and women will be an especially powerful tool to motivate and influence men to quit smoking within the homes and then to quit ultimately. If they express an interest to quit, they will be referred to the nearest urban primary health center for tobacco cessation. The influencers will be contacted again to encourage the smoker to quit smoking within home and to quit. Creating a movement and making “not smoking within the house an acceptable sociocultural norm” is the objective. At the end of the intervention as part of the dissemination activity smoke free homes declaration meeting for all community members in the presence of political leaders will be conducted.

*Control arm*: The other arm will get the standard of care which would include the routine programs which are being run by the government as part of the national tobacco control program such as training of health and social workers, NGOs, school teachers, and enforcement officers; Information, Education, and Communication (IEC) activities; school programmes; monitoring of tobacco control laws; coordination with Panchayath Raj Institutions for village level activities; and setting-up and strengthening of cessation facilities including provision of pharmacological treatment facilities at district level. Periodic assessments will be done at 10 and 16 months.

Health workers will conduct end-line surveys soon after the intervention and six months after the intervention in the intervention and control arm with the same questionnaire, urinary cotinine measurement and SHS measurement with an environmental sensor. Thus the measurements will be at 6, 10 months and 16 months respectively.

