### Sample size calculation

Based on previous studies we assume an ICC of 0.06.
^
43
^ To detect a minimal difference of 0.03ng/ml in cotinine levels between groups,
^
44
^ at 80% power with a two-sided alfa of 0.05, the estimated sample size was 113 indoor smokers per arm for individual randomization. Since one of the studies in the slum area of Ernakulam had found a prevalence of indoor smoking of 16% and considering slums above 100 households it is assumed that the expected number of smokers within household will be 20 per cluster with variability in clusters. Hence we estimated the sample size for unequal cluster size,
^
45
^ with a CV of 0.45 and VIF=2.4. The estimated sample size was 271 and 14 clusters per arm. Further we assumed a drop-out rate of 10%, the final sample size was rounded to 300 per arm and 15 clusters.

**
*Randomisation*
**

The trial has been registered in Clinical Trials Registry – India
CTRI/2021/06/034478.

A simple randomisation will be undertaken of the selected slums in the urban and peri-urban areas to receive intervention or not by a computer-generated random number list.

Allocation concealment: Allocation will be based on clusters and the allocation will be done after the baseline survey assessment by a statistician not directly related to the study. There is no allocation concealment. All the indoor smokers will be recruited and they will be selected before randomising clusters.

*Implementation*: Meetings will be conducted with the Kochi Corporation and District Medical Office regarding the objectives of the study. After the baseline survey, which will help to identify the indoor smokers, smoking practices, ventilation issues, and waste management practices, a simple randomisation will be undertaken of the selected slums in the urban and peri-urban areas to receive intervention or not.

The allocation sequence generation and the assignment of participants to the intervention will be carried out by the statistician and the investigators will enrol the participants.

*Blinding*: Blinding may not be possible as a lot of people are involved, local self-government officials, the investigators team, health centres, health workers, frontline workers such as the accredited social health activist, and anganwadi workers. The group of people who collect the outcome data will be blinded.

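### At month 10 the six-month recall for child respiratory morbidity reaches at least two months before allocation, pulling a minor secondary comparison toward no effect

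*Protocol article*

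**What the plan says.** All references are to the protocol article.

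- **Recall period.** Under Methods, Participants (Data collection), the child questionnaire covers "history of respiratory morbidity in the past 6 months and history of hospital admission". The six months clearly belong to respiratory morbidity. Whether they also govern hospital admission is not clear. The description of the spouse questionnaire gives no respiratory item and no recall period.
- **Reuse.** At the end of the Intervention section: "Health workers will conduct end-line surveys soon after the intervention and six months after the intervention", in both arms, "with the same questionnaire, urinary cotinine measurement and SHS measurement with an environmental sensor".
- **Timing.** The same place continues: "Thus the measurements will be at 6, 10 months and 16 months respectively". The Data collection text gives these three months for the air monitor and for cotinine as well.
- **Allocation.** Under Randomisation, "the allocation will be done after the baseline survey assessment by a statistician not directly related to the study".
- **Use of the item.** The Table 1 row "Resp. Infection" is ticked for child and woman at baseline and at both follow-ups, without a recall period. The secondary outcomes end with comorbidities; child respiratory illness is not named. The analysis text plans mixed models from baseline to each follow-up for each outcome indicator.
- **Length of the intervention.** The Intervention section says "In the initial two months of the intervention the SHG-ASHA team will conduct monthly home visits" and then describes two further months of visits. The abstract gives six months.

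No section gives a shorter recall period for the month-10 survey.

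**The concern.** The first follow-up comes four months after baseline, but the question looks back six. Part of what it collects at month 10 is therefore illness from before the clusters were allocated, which the intervention cannot have changed. Some of that illness may also have been reported at baseline, which adds correlation between the two visits that comes only from the overlap. What is at stake is the month-10 comparison of child respiratory illness: a real reduction would look smaller than it was, and a null result would be hard to interpret. Unless episode dates are recorded at interview, no later analysis can separate the two periods.

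**Working it through.** **Plan's own figures.** The article gives none for this outcome. Its one computed design figure, the cotinine sample size, reproduces: 1 + ((0.45² + 1) × 20 − 1) × 0.06 = 2.383, stated as 2.4; 113 × 2.4 = 271. The present point does not depend on it.

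**Inputs.** Recall of 6 months (Data collection); visits at months 6, 10 and 16 (Intervention); allocation after baseline, so not before month 6 (Randomisation).

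**Windows.** Window = visit month − 6 to visit month.

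| Visit | Window | Months before month 6 |
|---|---|---|
| Month 10 | 4 to 10 | 2 of 6 (33%) |
| Month 16 | 10 to 16 | 0 |

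If allocation falls later than month 6, the pre-allocation share at month 10 exceeds 2 of 6.

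**Overlap with the baseline window.** For a child interviewed at baseline in month b (b ≤ 6), the overlap is max(0, b − 4) months: 2 for b = 6, 1 for b = 5, none for b = 4 or earlier. The two or more pre-allocation months stay in the window whatever b is.

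**Illustration of the attenuation.** Assume counted episodes, a constant rate, even recall over the window and full effect from month 6. Then apparent rate ratio = (2 + 4 × RR)/6:

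- true 0.60: 4.4/6 = 0.73
- true 0.70: 4.8/6 = 0.80
- true 0.80: 5.2/6 = 0.87

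Under these assumptions 1 − RR shrinks by one third. If the effect starts only two months after baseline, the formula becomes (4 + 2 × RR)/6, and a true 0.70 appears as 5.4/6 = 0.90.

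The absolute difference in counts over the window is 4 × rate × (1 − RR), the same as a clean four-month window would give. What is diluted is the ratio and the difference per month of recall; the extra two months add only noise.

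**If the item is yes/no.** The formula above does not apply. Take an assumed control rate of 0.1 per month and RR 0.70:

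- question as stated: (1 − e^−0.60) − (1 − e^−0.48) = 0.451 − 0.381 = 0.070
- six months wholly after allocation: 0.108, so 35% is lost
- clean four-month window: 0.085, so 18% is lost

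Across assumed rates of 0.02 to 0.3 per month and RR 0.5 to 0.8, the loss is 34–44% against the six-month window and about 4–45% against the four-month window. The size therefore depends on the item format and on rates that the article does not give.

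**The case against.** The strongest case on the other side has four parts.

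1. **The follow-up form is not shown.** Reuse of the questionnaire cannot be wholly literal, since Table 1 collects demographics only at baseline and quitting only at follow-up. The month-10 stem might differ, and Table 1 does not say that its respiratory row is the six-month item. This lowers certainty. But the article states the window and its reuse and gives no exception for month 10.
2. **The outcome is small.** It is not named among the secondary outcomes except perhaps under comorbidities, and no hypothesis or sample size is attached to it. This stands and sets the weight of the point.
3. **The timing is in conflict.** If the abstract's six-month intervention were followed by a survey at month 12, the window would start at month 6 and the overlap would vanish. The calculation here follows the 6, 10 and 16 months given in the Methods. The passages need to be reconciled.
4. **Both arms are affected alike.** True: the result is attenuation and favours neither arm.

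A reader might infer more: that the effect is cut by exactly a third, that every early episode is counted twice, or that admissions and the woman's illness share the fault. The documents do not support these. The third needs a count item, a constant rate and immediate full effect. Double counting needs a baseline interview after month 4, and a door-to-door survey of 30 clusters may have started earlier. The six-month period is stated clearly only for the child's respiratory morbidity.

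**Conclusion.** The point holds for one item at one visit. On the schedule and reuse as stated, at least 2 of the 6 months recalled at month 10 precede allocation, and the comparison of child respiratory morbidity is pulled toward no effect. That conclusion needs only the stated recall, months and order of allocation. Its size is not fixed by the documents: a true 0.70 appearing as 0.80 is an illustration, and later onset would make the loss larger. Month 16 and the cotinine primary outcome are unaffected. This is a minor correction, worth making because the article reports that baseline collection is still under way, so on that status the month-10 form can still be changed.

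**What to change.** - **Question.** In the month-10 form, ask about child respiratory morbidity since a dated anchor at allocation or intervention start, using one common calendar date in both arms, or record the date of each episode. Anchoring to the child's own baseline visit is less good: with the survey spread over 30 clusters, it can still let in time before allocation.
- **Other items.** Do the same for hospital admission and the woman's respiratory item if they use a six-month window.
- **Analysis.** Compare the arms at month 10 on that window: with a person-time offset if episodes are counted, or as the proportion with any episode if the item is yes/no. Keep six months at baseline and month 16, so that baseline data already collected remain usable.
- **Text.** Reconcile the abstract's six-month intervention with the two-plus-two months and the month-10 survey in the Methods.

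The cost is one changed question stem and a line in the analysis plan. The downside is unequal recall lengths across visits, the same in both arms. For a yes/no item, the change from baseline to month 10 is then not on a common scale, so the between-arm comparison at month 10 should carry the inference.
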